### Evaluation of safety

The security evaluation concentrates on the frequency of negative occurrences. Participators will be asked to report any harmful occurrences. Adverse effects associated with acupuncture mostly include soreness, hemorrhage, bruising, empyrosis, blisters, infection, and disorientation. For security evaluation, all bad events, regardless of relation with acupuncture cure, are meticulously documented and evaluated by the researchers on the adverse event form at each assessment. This will encompass the time of happening, length of symptoms, seriousness (light, moderate, or critical), management strategies, solution time, and categorization of causality (definite, probable, unlikely).

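### All adverse events are recorded regardless of relation, but the stated three-level causality scale has no class for unrelated or possibly related events

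*Protocol article*

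**What the plan says.** All the relevant text is in the section Evaluation of safety of the Protocol article.

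- Safety focus: "The security evaluation concentrates on the frequency of negative occurrences".
- Recording scope: "all bad events, regardless of relation with acupuncture cure, are meticulously documented and evaluated by the researchers", on an adverse event form completed at each assessment.
- Items recorded: timing, duration, a three-grade severity, management, resolution and, last, "categorization of causality (definite, probable, unlikely".

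The causality list is not introduced as a set of examples. It has the same form as the severity list earlier in the same sentence, which reads as complete. No other section gives a fuller causality scale, defines the three classes, or says how to code an event that is unrelated or only possibly related.

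**The concern.** A form that takes every event will receive some that have nothing to do with treatment and some whose cause cannot be settled. The stated scale has a class for neither. The uncertain events matter more. With nothing between *probable* and *unlikely*, the assessor must choose a side, and no rule says which. The choice is made when the form is completed, so later analysis cannot recover a distinction that was never recorded.

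Uncertain cases are foreseeable here. The section lists infection and disorientation among the main adverse effects of acupuncture, and either can have another cause. At stake is whether the causality field can be interpreted, and with it any count of treatment-related events taken from it.

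**Working it through.** No stated figure depends on this point, so there is nothing to reproduce numerically. The check sets the recording scope against the listed classes.

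**Inputs** (all from Evaluation of safety): scope is all events, related or not; classes are definite, probable and unlikely; the safety focus is the frequency of events.

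**Step 1. Can each judgement be recorded as made?**

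| Assessor's judgement | Class on the stated scale | Consequence |
|---|---|---|
| Definitely related | definite | none |
| Probably related | probable | none |
| Possibly related | none; *probable* or *unlikely* | side depends on the assessor |
| Unlikely to be related | unlikely | none |
| Unrelated | none; nearest is *unlikely* | two classes merged, detail lost |

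Two of the five judgements have no class of their own. They do not have the same effect. Merging unrelated with *unlikely* keeps the event on the not-related side. A possibly related event can fall on either side.

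**Step 2. What happens to the two counts that could be reported?** Let *d*, *p*, *l* and *n* be the numbers of events judged definite, probable, unlikely and unrelated, and *u* the number judged only possible.

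- All events: *d* + *p* + *u* + *l* + *n*. Moving events between classes does not change this sum, so the stated safety focus is unaffected.
- Related events, read from the stated scale as definite plus probable: from *d* + *p* (every uncertain event coded down) to *d* + *p* + *u* (every one coded up).

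The width of that range is *u*. The article gives no event rates, so *u* cannot be estimated. It could be zero.

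**Step 3. Is a related-event count planned?** Neither Evaluation of safety nor Analytical statistics specifies one, and no comparison of related events between arms is described. Causality is nevertheless recorded for every event, so a related-event summary is a natural use of the field.

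**The case against.** The strongest reply is that the stated safety measure does not use causality. It is the frequency of all events, and the scale cannot alter that. No related-event analysis is planned, every event can be put in some class, and the number of levels is a matter of form design for which the article sets no standard. The adverse event form is not shown and may hold more detail.

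Much of this stands. All-cause frequency is untouched, and coding an unrelated illness as *unlikely* loses detail without turning it into a treatment-related event, so it would be too strong to say that such events are misclassified as related. Two things remain. The article does not leave the scale to another document: it states one, and that scale is too coarse for the scope set in the same sentence. Also, being able to place every event is not the same as placing it as judged, because an uncertain event is recorded as something the assessor did not conclude.

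A reader might go further and infer that the safety comparison between arms is biased. The arms differ in needling depth (about 20–25 mm against 5–8 mm), the section Blinding confines its explicitly masked assessor to efficacy, and events are judged by researchers for whom no masking is stated. The documents do not support that conclusion. Silence on masking does not show that the raters know the arm, and Blinding also sets out a separation of researchers, operators and statisticians. No comparison of related events is specified that could be biased. If unmasked safety rating were a problem, a longer scale would not cure it.

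**Conclusion.** The concern holds in a limited form. The stated causality scale does not match the stated recording scope: possibly related events must be pushed to *probable* or *unlikely*, and unrelated events cannot be told apart from *unlikely* ones. What becomes unreliable is the causality classification and any related-event summary built on it, by at most the number of uncertain events, which the documents do not allow one to estimate. All-cause event frequency, the efficacy outcomes and the sample size are not affected. Nothing in the documents supports a claim of bias between arms or a figure for its size.

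This rests on reading the three classes as the full list, as the wording suggests. If the form in use already has the extra classes, the point reduces to correcting the published list. It is a cheap improvement, not a threat to the trial's conclusions.

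**What to change.** In Evaluation of safety and on the adverse event form, list causality as definite, probable, possible, unlikely and unrelated. Before the first event is classified, define *related* as definite, probable or possible. State that all-cause event frequency by arm remains the main safety measure, with any related-event summary reported next to it.

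The cost is the wording of one form and one definition. The related-event count may read slightly higher, because uncertain events that could have been coded *unlikely* would now count as related. If events have already been classified on the three-level scale, those coded *probable* or *unlikely* would need to be classified again, so the change is cheapest before classification starts.

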### Ethical approval and study registration

The ethics committee has approved ethics (ZSLL-KY-2024-038-01) for the trial. Before signing up, investigators will overall tell to the participants the objectives of the study, the research project, its advantages, and invisible disadvantages. Objects will hold onto the full right to think whether to join in the trial, and must sign an informed consent form before being included in the study. Throughout the research process, stringent privacy safeguards shall be maintained, and all personal and medical information will remain secret. The protocol of trial has been filed in the Clinicaltrials registry with the identification code: NCT06401993.

### Gathering and managing data

Upon acquiring completed permission forms, data will be gathered from all participants. During the experiment, participant privacy will be rigorously safeguarded. Investigators must ensure the confidentiality of the subjects. Participants will get codes as identification. Their discretion will be guarded by the researchers. Objects will be nameless, and their messages and data shall be protected in case report forms. Paper records will be authenticated and input into a password-secured electronic database. Two data entry professionals will input all information into the computer database via double data entry to guarantee data correctness. Data confidentiality is maintained, with access restricted to approved researchers alone. Participants’ research information will remain confidential and will not be revealed outside the study without their explicit agreement.

### Study monitoring and quality control

Primary cultivation will be performed prior to subject recruitment to guarantee that all researchers and pertinent personnel comply with the study protocol, hence ensuring the quality of the study. Furthermore, all result evaluators will accept standardized cultivation to consistently perform outcome evaluations and fill out case report forms. Investigators will guarantee that all acquired data is accurate, thorough, and verifiable, sourced from original files. Investigators will convene quarterly monitoring assembly to address and resolve concerns that emerge throughout the study duration.

## Discussion

So far, the neurological processes behind acupuncture in the cure of tinnitus have not been definitively established. Nonetheless, recently, a growing number of neuroimaging studies have utilized advanced technologies such as ABR and fNIRS to quest the core mechanisms about basis of therapy of acupuncture in healing tinnitus. For instance, a study based on auditory brainstem response indicated that intervention with 2 Hz electroacupuncture can enhance the recovery of ABR auditory threshold shifts (35). Additionally, a study utilizing functional magnetic resonance imaging (fMRI) has shown that acupuncture excitement can mostly alleviate the ponderance of tinnitus in subjective tinnitus patients by reducing the functional connectivity of the amygdala (36). Recently, a trial based on fNIRS found that acupuncture can increase the concentration of HbO2 in the temporal lobe of tinnitus patients and affect the motivation about auditory cortex. Furthermore, significant activation was observed in the superior temporal gyrus after acupuncture, indicating that acupuncture can regulate the motivation of the auditory area in tinnitus patients (27). Indeed, the adjustment of idiographic brain cortices might be a target for the therapeutic effects of acupuncture and the neural mechanisms underlying tinnitus treatment. Functional connectivity denotes the statistical relationships or connections between activity in various brain areas. It indicates the extent of synchronization or coherence of neuronal processes among different brain areas. Functional connectivity analysis offers significant insights into the brain’s functional architecture in response to stimuli and alterations. It boosts a comprehensive knowledge of the processes via which acupuncture enhances brain function. Recently, fNIRS has attracted increased interest by investigating the impacts of acupuncture on cerebral zones and the dynamics of inter-regional functional connectivity. The prefrontal cortex (PFC) is an area of the cerebral cortex that covers the front part of the frontal lobe. The prefrontal cortex gets information from all other cortical areas and functions to arrange and guide physical, cognitive, emotional, and social behaviors. An fNIRS study observed that, compared to the control group, the network join with bilateral PFC as a node showed importantly improved functional join during acupuncture operation (37). With its noise-free operation and strong resistance to interference, fNIRS is better to other neuroimaging skills in studying the central mechanisms of tinnitus. Therefore, we have chosen fNIRS to validate the hypotheses of this study. Concretely, we hypothesize that compared to conventional acupuncture remedy, the “Dao qi tong luo” acupuncture skill will significantly alleviate tinnitus and correspondingly observe more pronounced changes in neural activity. This will provide profound insights into the fundamental mechanics of acupuncture in the remedy of tinnitus.

Indeed, the strength of our study stem from its innovativeness. For what I can tell, there has been alone one similar exploration that utilized fNIRS to investigate the neurological processes behind acupuncture in the treatment of tinnitus (27). However, the preceding research, serving as a pilot experiment, included just 18 individuals with tinnitus and lacked a randomized controlled design. Additionally, it focused specifically on HbO2 concentration as the fNIRS-related result. Secondly, in the process of evaluating the efficacy of acupuncture and moxibustion on chronic tinnitus patients, we used ABR as one of the evaluation indicators, which makes our evaluation indicators more objective. In contrast, the objective evaluation indicators for the previous RCT study of acupuncture and moxibustion treatment of chronic tinnitus are not clear. To address these prior shortcomings, our research is structured as a randomized, assessor-blinded controlled experiment. Given the novelty of fNIRS in tinnitus and acupuncture research, our findings are partly expected to shed light on the neural mechanisms underlying the effects of acupuncture on tinnitus. Furthermore, our study aims to provide objective methods for assessing the therapeutic effects of acupuncture on tinnitus.

While our study offers several innovative aspects and methodological strengths, it is not without limitations. Firstly, as a single-center study, the sample size may lack representativeness, which could potentially impact the reliability of the results. Secondly, the severity of tinnitus among participants was not restricted in our study. This variability could influence the outcomes, and therefore, prospective research should seek more participants with similar degrees of tinnitus severity to control for this variable and reduce its potential confounding effects on the study results. Thirdly, due to technical limitations, fNIRS can only measure the hemodynamics and neural activity in the superficial areas of the cerebral cortex, and it cannot capture the activities in deeper brain regions.

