## Materials and methods

### Study design

Our research is structured as a regulated and randomized trial with assessor blinding. Seventy-two participants who qualify with chronic tinnitus will be allocated in a 1:1 ratio to either the acupuncture group or the sham acupuncture group. Additionally, we will recruit 15 healthy individuals as subjects for data collection to compare the auditory brainstem response parameters and extracerebral oxygen levels of the cerebral cortex between chronic tinnitus patients and healthy subjects, and to observe the correlation of peripheral-central auditory function under different physiological states. Our protocol’s reporting complies with the Standard Protocol Items: Recommendations for Interventional Trials (SPIRIT) criteria. The SPIRIT for the study is shown in Figure 1, and the flowchart is shown in Figures 2, 3.

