#### Diagnostic criteria

Diagnosing tinnitus follows international criteria, which characterize it as the perception of sound without an external auditory stimulus. Additionally, according to the multidisciplinary European guidelines on tinnitus, tinnitus is referred to as “chronic” when its duration is 6 months or longer (2).

Unlike objective tinnitus, subjective tinnitus can only be perceived by the patient and cannot be assessed via auscultation by a physician.Patients perceive ear noises without the assistance of an outside source; these noises may be continuous or sporadic and can exhibit diverse auditory characteristics, including ringing, buzzing, clicking, or roaring.Otoscopic examination reveals no abnormalities in the ears, encompassing the eardrum and canal.Tinnitus affects the patient’s the norm of living to some extent, and the degree of annoyance varies from person to person.

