#### Inclusion criteria

Patients with chronic tinnitus, defined as a duration of the tinnitus of 6 months or longer (2).No contraindications for fNIRS scanning.Individuals aged between 20 and 55 years, who are right-handed.Patent external auditory canal and intact eardrum.The average hearing threshold in both ears is less than 35 dB.Normal expressive and comprehension abilities.

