#### Allocation concealment and randomization

Suitable participants will be assigned at random to the acupuncture group or the sham acupuncture group in a proportion of 1:1 using a random stratification block design by gender and lifetime, with the Statistical Product and Service Solutions Version 25.0 (SPSS Inc., Chicago, IL, USA). An impartial administrator, uninvolved in other study protocols, will conduct this process, and the details of the list of random allocations will remain completely confidential. This randomization results will be preserved in opaque, sealed, envelopes with sequential numbers to guarantee allocation concealment.

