### Outcome measures

Clinical Results: Clinical result metrics encompass the Tinnitus Handicap Inventory (THI), ABR testing, and fNIRS data collection. Evaluations will be carried out at baseline, after 10 treatment sessions.

THI score: The THI is a self-reported checklist that’s quick, simple. To manage and interpret, and covers a wide range of issues. It consists of 25 items, each scored from 0 to 4. An elevated THI indicates a more severe level of tinnitus.

ABR testing: The test records the peak latencies (PL), wave amplitudes, and interpeak intervals (IPL) of the subjects at various stimulation rates, as well as the differences in PL and IPL at the two stimulation rates (ΔPL and ΔIPL) to evaluate the function of the peripheral auditory nerve.

fNIRS data acquisition and processing: Cortical blood oxygen data will be collected to evaluate the central function of the subjects.

fNIRS results: fNIRS scans will be conducted at baseline, and after 10 treatment sessions. The blood oxygen concentrations measured include the concentrations of oxygenated hemoglobin (HbO), hemoglobin that has lost oxygen (HHb), and total hemoglobin (THb) in every measured channel.

fNIRS functional connectivity intensity: The intensity of functional connectivity between regions can quantify the relationships between routes or areas of interest within the fNIRS time plots. This is computed using the Pearson correlation coefficient between the average time series of any pair of channels of interest. The functional connectivity strength between channels of interest, as well as between channels of interest and other channels, is computed using NIRSKIT software. This software will help in analyzing the correlation between the time series data from different channels, providing insights into the connectivity patterns within the brain that may be associated with tinnitus and its treatment.

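### Baseline tinnitus severity is acknowledged as influential and is measured as THI, yet it is neither a stratification factor nor a named covariate, so precision is lost

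*Protocol article*

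**What the plan says.** All references are to the protocol article.

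- **Discussion, limitations.** The second of three limitations is that "the severity of tinnitus among participants was not restricted in our study". The authors expect this to affect results and ask later studies to enrol patients of similar severity "to control for this variable and reduce its potential confounding effects on the study results".
- **Allocation concealment and randomization.** Patients are assigned by a "random stratification block design by gender and lifetime". The second factor is not defined; age is the likely meaning. Severity is not a factor.
- **Study design.** "Seventy-two participants who qualify with chronic tinnitus will be allocated in a 1:1 ratio", which gives 36 per arm.
- **Diagnostic and inclusion criteria.** The inclusion criterion for tinnitus concerns duration: "Patients with chronic tinnitus, defined as a duration of the tinnitus of 6 months or longer". The diagnostic criteria say that tinnitus affects the patient's life "to some extent, and the degree of annoyance varies from person to person". No THI level is set.
- **Outcome measures.** THI is assessed at baseline and after 10 sessions. "It consists of 25 items, each scored from 0 to 4", so the range is 0 to 100 and a higher score is worse.
- **Analytical statistics.** Clinical scores, ABR parameters and fNIRS data are compared between arms by t-tests at a two-sided 0.05 level. No baseline covariate is named.

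**The concern.** The plan identifies a baseline variable that it expects to matter, measures it in every patient, and then uses it in neither the allocation nor the stated comparison. It treats restricting severity as the remedy and postpones that to another trial. Two remedies that need no restriction are open to this one: stratified randomisation, which is already in use with other factors, and covariate adjustment.

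THI is the trial's only symptom score. With 36 per arm, a baseline gap of several points can arise by chance. If it does, a reader of an unadjusted comparison cannot tell how much of the end-of-treatment difference was there at the start, and the article itself will have pointed to severity as the suspect. Even without a visible gap, between-patient variation in severity stays in the error term and reduces power.

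**Working it through.** **Inputs from the article:** 72 patients, 1:1, so 36 per arm; 30 per arm evaluable (Sample size estimation, where 30 × 1.20 = 36); two-sided alpha 0.05; power 80%.

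**Assumptions:** the article gives no SD for THI and no correlation between baseline and end-of-treatment THI. Results are therefore in SD units, with SD 15–25 points for illustration. The correlation r is taken as 0.5–0.7, and baseline THI as roughly normal.

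The article states no figure for imbalance or precision, so there is none to reproduce. The 30 per group cannot be re-derived because the two rates in its formula are not given. Nothing below depends on how it was obtained.

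**1. Chance imbalance as planned.** The SE of the baseline mean difference is SD × √(2/n).
- 36 per arm: √(2/36) = 0.236 SD. For a gap above 0.3 SD, 0.3/0.236 = 1.27, so P = 20%.
- 30 per arm: √(2/30) = 0.258 SD and P = 25%.
- The 95% range at 36 per arm is ±1.96 × 0.236 = ±0.46 SD. That is ±6.9, ±9.2 and ±11.5 THI points at SD 15, 20 and 25.

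These figures ignore any indirect balance gained through gender or age.

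**2. Imbalance with THI as a stratification factor.** A median split leaves a within-half variance of 1 − 2/π = 0.363.
- Ideal case: SE = √(0.363 × 2/36) = 0.142 SD. Then 0.3/0.142 = 2.11, so P = 3.5%.
- Simulated with real blocks: about 4% with THI as the only factor. With three two-level factors in blocks of 4 or 6 it is about 5% at the median, and 7–12% if the cut falls at the 20th–30th percentile.

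For a reasonable cut, roughly 4–10% is a fair summary.

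**3. Error rate of the planned t-test.** Under no treatment effect, 40,000 simulated trials with 30 per arm and r = 0.5 or 0.7 gave type I error of 0.051 on end scores and 0.050–0.051 on change. In the roughly 5% of those trials with a baseline gap above 0.5 SD, the false-positive rate was 18–31% on end scores and 13–19% on change. The test is valid on average, but hard to interpret once an imbalance has occurred.

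**4. Precision recovered by adjustment.** ANCOVA multiplies the variance of end scores by 1 − r².
- r = 0.5: 1 − 0.25 = 0.75, a 25% reduction.
- r = 0.7: 1 − 0.49 = 0.51, a 49% reduction.

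The difference detectable with 80% power at 30 per arm is (1.96 + 0.84) × √(2/30) = 0.72 SD unadjusted. Multiplying by √0.75 and √0.51 gives 0.63 and 0.52 SD.

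The article does not say whether the t-test is on end or change scores. A change score has variance 2(1 − r) = 1.00 at r = 0.5 and 0.60 at r = 0.7. Against that, the reduction is 25% (0.75/1.00) or 15% (0.51/0.60).

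**5. Why stratifying alone is not enough.** Stratifying removes between-half variation from the true variance of the treatment difference, but an unadjusted t-test still counts it. With a median split the true variance of the end-score difference is 1 − 0.637r² times what the test assumes.
- r = 0.5: 1.96/√0.841 = 2.14, so the actual two-sided error is about 3.3%.
- r = 0.7: 1.96/√0.688 = 2.36, so it is about 1.8%.

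The test becomes conservative and the gain is partly wasted unless the analysis adjusts as well.

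**The case against.** The strongest reply is that this is a disclosed design choice, not an error. Allocation is randomised, stratified and concealed; chance imbalance is already covered by the t-test's 5%; and a statistical analysis plan that is not shown may adjust for baseline THI. Much of this stands. The point concerns efficiency and interpretability, not validity, and a missing covariate alone would be a weak finding. But an analysis plan cannot change the stratification factors, which the article fixes, and disclosing a limitation does not control it when the means are at hand.

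It is also fair that 3.5% is a best case, that a 0.3 SD gap carries into end scores only as r × 0.3 (0.15 SD at r = 0.5), and that ANCOVA alone would recover most of the precision without a new list. Stratification adds protection against a visible imbalance; adjustment does more for power.

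A reader might infer three stronger things that the article does not support:

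- **That severity is the main confounder.** The Discussion lists it second of three limitations and calls the confounding only potential.
- **That the comparison is biased.** Chance imbalance after randomisation is not systematic confounding, and step 3 shows the overall error rate intact.
- **That some patients cannot improve, so a minimum THI is needed.** A score cannot fall only at 0. The diagnostic criteria mention some effect on the patient's life, which makes 0 unlikely though it does not exclude low scores. The share of low scorers is unknown, so any figure for power lost at the floor would rest on invented proportions. A minimum THI would also narrow the population and might weaken the planned correlations of THI with ABR and fNIRS. That is an eligibility trade-off for the investigators, not a defect.

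**Conclusion.** The point holds as a specific and inexpensive improvement. The plan names severity as influential, measures it, and makes no stated use of it in allocation or in the THI comparison. At 36 per arm the chance of a baseline THI gap above 0.3 SD is about 20%, against roughly 4–10% with blocked stratification on THI. Adjusting for baseline would cut the residual variance of end scores by about 25–50%, and by less if the unadjusted test was to be on change. Type I error is not inflated overall.

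The imbalance figures rest on roughly normal baseline THI and, for the stratified case, on where the cut falls. The precision figures rest on an assumed correlation of 0.5–0.7 that the article neither gives nor contradicts.

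**What to change.** 1. **Allocation concealment and randomization.** For patients not yet randomised, make baseline THI a stratification factor: below, or at or above, a pre-set cut near the expected median. Require THI to be completed before the envelope is opened. Three two-level factors give 8 strata of about 9 patients (72/8). If that is too thin, let THI replace gender or lifetime, which gives 4 strata of about 18.
2. **Analytical statistics.** Compare end-of-treatment THI between arms by ANCOVA with baseline THI (as a continuous score) and the stratification factors as covariates, in place of the t-test. This applies to all patients, including any randomised under the existing list.
3. **Discussion, limitations.** State that severity is not restricted but is controlled by stratification and adjustment.

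The cost is a new allocation list, an amendment and somewhat thinner strata. No extra measurement is needed and eligibility does not change. If a new list is no longer practical, item 2 alone recovers most of the precision.
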